## Abstract

**Background:**

Over 55 million adults are living with dementia globally, which is projected to reach 157 million by 2050. Mild cognitive impairment (MCI), a syndrome of memory impairment with intact activities of daily living, may precede dementia by several years. Around 5–15% of individuals with MCI convert to dementia annually. Novel treatments which delay progression of MCI to dementia are urgently needed. Transcutaneous vagal nerve stimulation (tVNS) is a non-invasive neuromodulation technique that targets the vagus nerve. Importantly, tVNS has been shown to improve cognition in healthy volunteers, but has not been extensively examined as a potential therapeutic approach in MCI. VINCI-AD will examine the safety and feasibility of tVNS in older adults with MCI.

**Design:**

VINCI-AD is an investigator-led, single-site, single-blind, sham-controlled crossover pilot study which aims to assess the safety and feasibility of tVNS in 40 participants with amnestic MCI. All participants will attend for three consecutive study visits during which they will be randomised to receive no stimulation (baseline), active tVNS stimulation (stimulation at cymba conchae of left ear) or sham tVNS stimulation (at earlobe). Safety will be primarily assessed by ascertainment of adverse events. Further safety assessment will examine the impact of acute tVNS on subjective (orthostatic symptoms), peripheral (finometry-based blood pressure) and central (assessed via Near Infrared Spectroscopy [NIRS]) haemodynamic responses to active stand. Feasibility will be determined using a custom-designed occupational assessment of device usability. Exploratory secondary analysis in VINCI-AD will examine the potential impact of acute tVNS on associative memory, spatial memory and inhibitory control to inform sample size estimates for future trials of tVNS in older adults with MCI.

**Discussion:**

VINCI-AD will report on the safety (adverse events/haemodynamic responses to active stand) and feasibility of tVNS as a potential therapeutic option in MCI. Detailed reporting of study eligibility and completion rates will be reported. Exploratory analysis will examine the potential cognitive benefits of acute tVNS on cognitive function in MCI to report potential effect sizes that may inform future clinical trials in this cohort.

**Trial registration:**

https://clinicaltrials.gov/ct2/show/NCT05514756. Trial Registration Number NCT05514756 (24th August 2022 for this protocol, version 1.0.)

**Supplementary Information:**

The online version contains supplementary material available at 10.1186/s12883-023-03320-5.

## Background

Mild Cognitive Impairment (MCI) is a clinical syndrome characterised by cognitive impairment and deficits on neuropsychological testing, with intact activities of daily living [1, 2]. Typical estimates suggest a 5–15% conversion rate to dementia per year in those with MCI [4, 5]. Targeting individuals at high-risk for dementia, such as those with MCI, may represent an important strategy for non-pharmacological interventions targeted at dementia prevention. One such approach which has shown promise in MCI is through non-invasive brain stimulation [3].

Vagus Nerve Stimulation (VNS) involves electrically stimulating the vagus nerve (VN) either directly using implanted VNS (iVNS) devices to directly stimulate the cervical VN or using novel transcutaneous VNS (tVNS) devices. Importantly, tVNS devices are portable, handheld, relatively inexpensive and do not require surgery for implantation. tVNS devices pulse electricity gently through the skin in specific areas (such as the cymba conchae of the external ear) which have extensive VN afferent branches [4]. This has been shown to modulate subcortical and cortical activity even with relatively short burst of stimulation and may have beneficial effects on cognitive function [5–8].

Improved cognition has been noted in populations treated with iVNS for epilepsy and depression since its approval by the FDA [9–16] A one -year pilot study found that iVNS devices stabilised or improved cognitive performance in participants with Alzheimer’s disease [17, 18]. In non-clinical populations, tVNS has been shown to exert cognitive benefits across several domains including emotional recognition, post-error slowing and lexical fluency [19–26]. However the most consistent cognitive improvement in healthy populations based on meta-analytic evidence has been for executive function [27].

Older adults with MCI and dementia are at increased risk for Neuro-Cardiovascular Instability (NCVI) and Orthostatic Hypotension (OH) [28, 29]. NCVI/OH may even influence clinical progression and mortality in those with cognitive impairment and dementia [30, 31]. The VN is the primary mediator of neuro-cardiovascular reflexes including the baroreceptor response that maintains cerebrovascular perfusion during systemic hypotension [35]. Given the prominent role of the VN in NCVI, it is crucial to understand the effect of VN modulation on NVCI phenotypes in older adults with MCI, who may be at greater risk of OH and other NCVI phenotypes. Whilst VN stimulation may exert beneficial effects on NCVI, it is of paramount to establish its safety in older adults with MCI. Key measures to assess the neuro-cardiovascular response to acute tVNS stimulation include: measurement of Heart Rate Variability (HRV) – a marker of VN activity, peripheral (finometry based beat-to-beat blood pressure assessment) and central (assessed via Near Infrared Spectroscopy [NIRS]) responses to active stand.

Vagally-mediated transient reductions cerebral perfusion in those with MCI could be deleterious, as those with MCI have reduced cerebral blood flow compared to Cognitively Unimpaired (CU) individuals at baseline [32]. tVNS, however, specifically exploits the peripheral anatomy of the VN, and it is the right cervical VN that provides most negatively chronotropic effects via the sinoatrial node. Hence only the cymba conchae of the left ear is stimulated during tVNS, as the left VN provides cardiac innervation via the atrioventricular node which is less likely when stimulated to cause bradycardia [33, 34].

Oxygenation of cerebral tissue can be noninvasively measures using tools such as NIRS devices. NIRS devices project near-infrared light into underlying tissue (such as cerebral cortical tissue) and measures the backscatter of this light using detectors. Based on the amount of backscatter, the concentration of oxygenated haemoglobin and deoxygenated haemoglobin can be determined and from this information the Tissue Saturation Index (TSI; a measure of tissue oxygenation) can be determined [35]. The TSI has emerged as an objective surrogate marker of cerebral perfusion, suitable for clinical testing of dynamic cerebrovascular hemodynamics during standing [36] and has been evaluated as a marker of oxygenation during tVNS and cognitive testing as well [37]. There is a known age-related reduction in resting-state TSI in the prefrontal cortex in older adults [38] and persons with MCI have lower resting state TSI levels compared to healthy controls [39, 40]. Whether frontal TSI could be augmented by tVNS in a population with MCI remains to be explored.

The Vagus Nerve Stimulation in Mild Cognitive Impairment (VINCI-AD) study will examine the use of an easy-to-use, tVNS device in MCI. VINCI-AD will determine the safety (adverse events ascertainment, peripheral and central haemodynamic responses to active stand) and feasibility of tVNS as a potential treatment in older adults with MCI. Pre-specified exploratory secondary analysis will assess the impact of acute tVNS on cognitive function (namely associative memory, spatial memory, inhibitory control, language and working memory) to provide potential effect size estimates to inform future clinical trials of tVNS in MCI.

## Methods/design

### Study design

VINCI-AD is a single-site, single-blind, sham-controlled crossover pilot study in patients with amnestic MCI. Each participant is assessed at baseline (no stimulation) followed by randomisation to both sham stimulation and active tVNS stimulation over two subsequent study visits. The study comprises a baseline assessment (visit 1) followed 7–10 days later by either an active or sham stimulation study visit and again 7–10 days later by a third visit wherein the final condition (active or sham) will be undertaken. The inclusion of a sham stimulation condition is to confound for potential unblinding, which is common in device trials. Participants will be enrolled and consented by study clinician (HD). Please see Fig. 1 for an illustration of randomisation and sham stimulation technique.

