### Pre-specified exploratory analysis

#### Potential effects of acute tVNS on cognitive performance

VINCI-AD is a safety and feasibility study of tVNS device use in individual with MCI. Exploratory secondary analysis will also assess the potential benefits of acute tVNS on cognitive performance. Cognitive function will be assessed under identical conditions in all participants at all three visits and will encompass assessment of the following:

Face Name Association Task (FNAT): A cross-modal associative memory test [45, 46] hosted on E-PRIME (Psychology Software Tools, Sharpsburg, USA). The participant is shown 30 face-name pairs. After a brief interlude (less than one minute) participants are then shown a combination of faces, some of which have already been displayed. The assessment involves both accurate recognition of recently displayed faces and correct recall of associated names. tVNS has been shown to boost associative memory as assessed by this task in CU older adults [47] but has not been assessed in those with MCI.Sustained Attention to Response Task (SART): A computer based response inhibition task [48] hosted on E-PRIME (Psychology Software Tools, Sharpsburg, USA) This is similar to Go/No-Go or Stop/Signal tasks whereby participants are required to withhold response to a single, infrequent target (the digit 3) presented amongst a background of frequent non-targets (0–2, 4–9) to which the participant does respond by pressing the space key on the computer keyboard.SeaHero Quest ™ the electronic tablet-based app Sea Hero Quest (GLITCHERS © London, UK; University College London, London, UK) will be used whereby participants will be asked to complete 5 levels of increasing complexity of a nautical-themed navigation task designed to assess speed and accuracy of navigating a boat to a map target [49, 50].Language assessments will include list learning, semantic fluency, list recall and list recognition assessments adapted from RBANS battery as tVNS has demonstrated benefits in these domains in both healthy [26, 51] and clinical populations [11, 12].Working memory will be assessed via digit span forward and backward which will be undertaken as part of the adapted RBANS battery.

Participants will wear the portable NIRS analysis device during all cognitive tasks so that the TSI may be measured continuously during cognitive tasks at baseline, during active and during sham stimulation.

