### Randomisation

Patients who provide informed consent to participate and who fulfil eligibility criteria will be enrolled into the study. Initial visit (visit 1) involves baseline assessments of neurocardiovascular, cognitive, and inflammatory status. Participants are then randomised to either active or sham stimulation condition at the following visit and then to the alternate condition at the final visit. Participants are blinded to the active or sham stimulation condition but study researchers are not (i.e. single-blinded). Please see Fig. 1 for randomisation strategy.

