### Sample size

To establish the safety and feasibility of tVNS in a population of older adults with MCI, VINCI-AD aims to recruit 40 participants for inclusion. This sample size is based on previous literature which investigated the effects of tVNS in healthy young adults [19–21, 23, 55] and also CU older adults [47]. Potential effect sizes from the results of this feasibility study will inform an accurate power calculation for future definitive trials.

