### Statistical analysis

VINCI-AD will assess the safety and feasibility of tVNS in older adults with MCI. All participants will be included in final analysis in an “intention-to-treat” fashion. Statistical analysis will be conducted using MATLAB (The MathWorks, Inc., Natick, MA, USA), SPSS (IBM SPSS Statistics for Windows, Armonk, NY: IBM Corp) and GraphPad Prism (GraphPad Software, Inc., San Diego, CA, USA). We anticipate that TSI analysis will require cleaning to remove “noisy” channels i.e. removing large spikes (changes in oxy-Hb larger than 0.5 mM/mm in amplitude); noisy channels will be excluded from analyses and data analyses will utilise software Platform for Optical Topography Analysis Tools [56] with a bandpass filter with cut-off frequencies of 0.01–0.8 Hz to remove instrumental or physiological noise [57].

In the first instance, descriptive statistics will be described for the cohort, reported as means (with standard deviations) or medians (with inter-quartile ranges) and proportions (percentages) as appropriate.

The primary aim of the current study is to assess the safety and feasibility of tVNS in MCI. To assess safety, a chi-square test will compare the number of adverse events reported during the active vs. sham condition. Further safety assessment will elicit symptoms experienced during active stand (using a chi-square statistic), peripheral (beat-to-beat blood pressure response to orthostasis – using mixed-effects linear regression with study condition as the independent variable, with random intercepts for study participant) and central (TSI – also assessed using a linear mixed-effects model). Feasibility will be reported via recruitment rates, successful enrolment, and study completion in proportions and percentages. Tolerability will be assessed using Likert scales, which will be compared between active and sham conditions using paired between-condition statistics (t-test if normally distributed or non-parametric equivalent). Descriptive statistics will be used to report acceptability using the modified Kettle test.

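### No stimulation is always Visit 1, so any comparison with it is confounded with visit order; active minus sham should be named as the stimulation effect, and the abstract corrected

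*Protocol article*

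**What the plan says.** **Order of conditions.** Study design in the protocol article fixes the sequence: "Each participant is assessed at baseline (no stimulation) followed by randomisation to both sham stimulation and active tVNS stimulation over two subsequent study visits". The second visit comes after the baseline visit, "followed 7–10 days later by either an active or sham stimulation study visit", and the third 7–10 days after that. The Randomisation section agrees, since randomisation follows Visit 1: "Participants are then randomised to either active or sham stimulation condition at the following visit". Table 1 shows the same layout. The Design paragraph of the abstract differs. It describes "three consecutive study visits during which they will be randomised to receive no stimulation (baseline), active tVNS stimulation" or sham, so no stimulation appears as one of the randomised conditions.

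**Measurements.** The section on cognitive performance says: "Cognitive function will be assessed under identical conditions in all participants at all three visits". Table 1 also places the active stand with tissue saturation index (TSI), heart rate variability and cytokines at all three visits.

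**Analysis.** Under Statistical analysis, beat-to-beat blood pressure is modelled "with study condition as the independent variable, with random intercepts for study participant". TSI also gets a linear mixed model, with no terms listed. Cognition, heart rate variability and inflammatory markers get a repeated three-way ANOVA, or a non-parametric test, with Bonferroni correction; the factors are not listed. Adverse events and Likert tolerability are compared between active and sham only.

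**Use.** The Sample size section says: "Potential effect sizes from the results of this feasibility study will inform an accurate power calculation for future definitive trials".

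**The concern.** A condition that everyone receives first shares its place with first exposure to the tests, the stand procedure and the clinic. If performance improves with repetition, or physiology drifts or habituates between visits, that change appears in active minus none and sham minus none as if stimulation had caused it.

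The Discussion lists the three time points as a strength for inference and does not mention practice. The article never says which contrast will supply the cognitive effect size. If a later trial were sized on an overall or baseline-referenced effect that contained practice gain, its assumed effect would be too large and the trial too small. The abstract adds to the risk by presenting no stimulation as a randomised comparator.

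**Working it through.** **The plan's own figure.** The 40 participants cannot be reproduced, because the article rests the number on earlier literature and gives no effect size, SD, alpha or power. The check therefore asks what the design can estimate, and how large the distortion could be.

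**1. Estimability.** There are two sequences: none–active–sham and none–sham–active. A model with an intercept, indicators for active and sham, and indicators for Visit 2 and Visit 3 has 5 columns. In every row, active + sham = Visit 2 + Visit 3 (0 at Visit 1, 1 afterwards), so the rank is 4. Active minus none and sham minus none are not estimable. Active minus sham is. Adding a visit term cannot rescue the contrasts with no stimulation.

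**2. Overall three-condition test, equal gain g at Visits 2 and 3.** Inputs: n = 40 (Sample size section). Assumed: true stimulation effect zero, within-person correlation ρ = 0.5 or 0.7, total SD 1, α = 0.05. The condition means are 0, g, g, with squared deviations summing to (2/3)g². The noncentrality is λ = 40 × (2/3)g² / (1 − ρ), for an F test on 2 and 78 degrees of freedom.

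| g (SD) | λ, ρ = 0.5 | rejects | λ, ρ = 0.7 | rejects |
|---|---|---|---|---|
| 0.1 | 0.53 | 9% | 0.89 | 12% |
| 0.2 | 2.13 | 23% | 3.56 | 36% |
| 0.3 | 4.80 | 47% | 8.00 | 70% |
| 0.5 | 13.33 | 90% | 22.22 | 99% |

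**3. Simulation with a slightly larger gain at Visit 3.** 10,000 runs per setting, 20:20 sequence split, true stimulation effect zero. The expected spurious active minus none is the mean of the two gains, for example (0.2 + 0.3)/2 = 0.25 SD. Ranges run from ρ = 0.5 to ρ = 0.7.

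| Gain at Visit 2 / Visit 3 (SD) | Overall test rejects | Spurious active minus none | Bonferroni active vs none rejects (nominal 1.7%) |
|---|---|---|---|
| 0.1 / 0.15 | 11.5–16.5% | about 0.12 SD | 5–8% |
| 0.2 / 0.3 | 33–53% | about 0.25 SD | 19–32% |
| 0.3 / 0.4 | 61–83% | about 0.35 SD | 40–64% |
| 0.5 / 0.6 | 95–99.7% | about 0.55 SD | 83–97% |

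Sham minus none carries the same bias.

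**4. Active versus sham in the same runs.** Across these four settings at a 20:20 split there is no bias, and the Bonferroni test rejects in 1.3–1.8% of runs. At 24:16 without a period term the bias is (24 − 16)/40 × the Visit 2-to-3 change, so at most 0.2 × 0.1 = 0.02 SD. With period in the model, rejection at the 5% level is 4.6–5.5% and the estimate is unbiased at both splits.

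**5. Precision without a period term.** With balanced sequences and a Visit 2-to-3 change of π SD, the variance of the active–sham difference is inflated by 1 + π²/(2(1 − ρ)). For π = 0.05 and ρ = 0.5 this is 1 + 0.0025/1 = 1.0025. For π = 0.1 and ρ = 0.7 it is 1 + 0.01/0.6 = 1.017. With the increments used in step 3, the loss is under 2%.

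**The case against.** The strongest reply is that the trial is sham-controlled and the article nowhere says that active minus none will be reported as the effect of stimulation. Bonferroni comparisons among three conditions would include active versus sham, and practice would show equally in sham versus none, where an alert reader would recognise it. This stands. A reader might infer that practice effects *will* be reported as stimulation effects; the documents show only that the plan leaves this open.

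A reader might also infer that the models contain condition and nothing else. The documents do not settle that. The three-way ANOVA has no listed factors, the TSI model has no listed terms, and the levels of condition are not spelled out for blood pressure. Three conditions is the natural reading because these outcomes are taken at all three visits. A condensed article may leave a period term to a fuller document, so its absence is not a finding in itself. But step 1 shows that no such term could separate no stimulation from Visit 1.

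The size of practice is assumed. Participants have amnestic MCI, and alternate test forms are neither stated nor excluded. At the small end (0.1/0.15 SD) the overall test rejects in only 11.5–16.5% of runs. For blood pressure, TSI, heart rate variability and cytokines, even the direction of any drift is unknown.

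Finally, cognition is labelled exploratory in a safety and feasibility pilot. That lowers the severity, but these effect sizes are still meant to inform later trials.

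**Conclusion.** The point holds in limited form and should be fixed. The aliasing of no stimulation with Visit 1 follows from the design and needs no assumption, and the abstract contradicts the Methods on what is randomised. That the planned overall test is affected rests on the three-condition reading.

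The size depends on assumed practice: for equal gains of 0.1 to 0.5 SD, correlation 0.5 to 0.7 and 40 participants, false rejection by the overall test runs from about 9% to 99%. This quantified harm concerns the exploratory cognitive outcomes. For the haemodynamic safety models the same aliasing exists, but no size or direction can be given.

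Two stronger inferences fail. The randomised active–sham contrast is not materially biased by a missing period term (at most about 0.02 SD in the settings tried). A large loss of precision would need a large Visit 2-to-3 change: 42% requires 0.5 SD at correlation 0.7 (1 + 0.25/0.6 = 1.42), and nothing in the documents supports a change of that size. The adverse-event and Likert comparisons do not use Visit 1 and are unaffected.

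**What to change.** 1. In Statistical analysis, name active minus sham at Visits 2 and 3 as the stimulation effect, estimated from a mixed model with condition and period as fixed effects and participant as a random effect.
2. In Sample size, state that this estimate, with its 95% CI, is what will inform the sizing of later trials.
3. Use Visit 1 descriptively or as a covariate. State that any comparison with no stimulation is confounded with visit order.
4. Correct the abstract so that no stimulation is the fixed first visit and only the order of active and sham is randomised.

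The cost is wording, one degree of freedom for period, and weaker language for comparisons with baseline. No new visits or data are needed.

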**Fig. 1 Fig1:**
[figure not shown]
Method of crossover

Our study will follow the Standard Protocol Items: recommendations for Interventional Trials (SPIRIT) guidelines [41]. Table 1 illustrates the SPIRIT flow diagram summarising study procedures, outcome measures, randomisation and assessments for each study visit.

**Table 1 Tab1:** Flowchart of VINCI-AD Protocol Timeline

			Study Period					
			Screening (day − 90 to day − 7)	Visit 1 (day 0)		Visit 2 (day 7–10)		Visit 3 (day 14–17)
Enrolment								
- Eligibility Screen			x					
- Informed Consent			x					
Intervention								
- Baseline assessments (no stimulation)				x				
- Active (left cymba conchae) stimulation						ø		ø
- Sham (left earlobe) stimulation						†		†
Assessments								
- General assessment, vitals, medication changes				x		x		x
- Primary Outcome: Safety								
- Assess for AE/ SAEs						x		x
- Active stand with TSI				x		x		x
- Primary Outcome: Acceptability and Tolerability								
- Likert scale questionnaires						x		x
- Cognitive assessments								
- FNAT				x		x		x
- SART				x		x		x
- SHQ				x		x		x
- Verbal word learning				x		x		x
- Semantic fluency				x		x		x
- Digit span forwards				x		x		x
- Digit span backwards				x		x		x
- Verbal word recall				x		x		x
- Verbal word recognition				x		x		x
- Frontal Oxygenation								
- Cognitive testing TSI				x		x		x
- Neurocardiovascular assessments								
- HRV				x		x		x
- Serum / Plasma venepuncture								
- Inflammatory cytokine panel				x		x		x
- Device usability assessment								
- Kettle test								x

Ø = active stimulation randomisation: participant randomised to either sham or active stimulation at Visit 2 and alternative stimulation site at Visit 3

† = sham stimulation randomisation: participant randomised to either sham or active stimulation at Visit 2 and alternative stimulation site at Visit 3

AE – Adverse event; SAE – Serious adverse event; FNAT – Face Name Association Task; SART – Sustained Attention Response Task; SHQ – Sea Hero Quest Tas; NIRS – functional Near Infrared Spectroscopy; HRV – Heart Rate Variability; TSI – Tissue Saturation Index

